### Interventions

Following baseline assessment, the participant will be randomized to control arm (usual care), mailed video only, or video plus *promotora* outreach, as described below.

#### Control arm

Participants who are allocated to the control arm (‘Usual Care’) will not receive any motivational messages or intervention materials from study staff. Usual care entails any information on the importance of regular Pap tests for cervical cancer risk reduction provided routinely by clinic staff to all women at community clinics.

#### Low intensity intervention (video)

Participants will be mailed a culturally-appropriate Spanish-language video with information and encouragement to undergo cervical cancer screening, information about resources to pay for screening, and other practical assistance such as resources for transportation. This intervention consists of a 13 minute video presentation of three different generational women talking in Spanish about their experiences and concerns for cervical cancer screening in the form of a “novela” or soap opera. The video has English subtitles for monolingual English-speaking participants. The video was developed as part of the ‘Ayudando a Las Mujeres con Informacion, Guia y Amor para su Salud’ (AMIGAS) intervention, which consisted of a lay community health educator or *promotora de salud*-(*promotora)* led in-home education session, and a video presentation. The culturally appropriate, theoretically-based curriculum was developed using a community-based participatory research approach, with the aim of increasing the uptake of cervical screening for Hispanic women living along the U.S./Mexican border [14].

#### High intensity intervention (video plus *promotora* outreach)

In this arm, women will receive a high-intensity intervention that includes *promotora*-led in-home education session. The educational session will include the culturally-appropriate video (as used in the low intensity intervention) [14], a “promise sheet” (i.e., a sheet that a woman signs to indicate what she will do next, such as thinking about having a Pap test, making an appointment), and a resource sheet which lists resources such as contact information for community resources for transportation, childcare, and other potential barriers for successful attendance at clinic. The *promotora* will have the opportunity to have a conversation about cervical cancer screening and directly schedule a Pap test for women through the clinic. For women who are not yet ready to schedule a Pap test, the *promotora* will make a telephone call to the woman two weeks later to review the action steps, and assess readiness to schedule a Pap test.

A *promotora* will be recruited by YVFWC from the community and will be provided with an initial training session lasting three days, which addresses procedures for approaching households and delivering the intervention, cervical cancer screening facts and tracking and documentation procedures. Other studies indicate *promotora* outreach to be a successful approach for Hispanic women [15-18].

Both the video and *promotora* led intervention are part of an educational curriculum created to increase cervical cancer screening in Hispanic women; the curriculum is based in Social Cognitive Theory (SCT). Definitions of social cognition vary, but central to the theory is that people’s social behavior can be understood by examining their beliefs about their behavior in a social context; and that people learn not only from their own experiences, but by observing the actions of others. According to SCT, three main factors, self-efficacy, goals and outcome expectancies, affect the likelihood of changing a health behavior [19,20].

### Primary outcome

The primary outcome is defined as completion of a Pap test within 7 months after baseline assessment. Participants will be tracked via medical record review at YVFWC. Differences in Pap testing rates in intervention and control arms will be assessed. Cost-effectiveness analysis will examine the associated costs per woman screened, by intervention arm.

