The aims of the Cervical Cancer Screening and Adherence to Follow-up Among Hispanic Women study are threefold: (1) to determine the effect of two different intensity, culturally appropriate information based interventions on Pap test utilization, vs. control; (2) to determine whether a patient navigator program can improve adherence to follow-up after a diagnosis of an abnormal Pap test, in a sample of Hispanic women in Yakima and Franklin counties of Washington (WA) State, US; and (3) to assess the cost-effectiveness of each of the intervention programs.

The study will be implemented with the aid of the two community based partners, the Yakima Valley Farm Workers’ Clinic (YVFWC) which operates a network of 13 federally qualified health center clinics in Eastern Washington specializing in the delivery of primary care services to low-income Latinos; and the Breast, Cervical, and Colon Health Program of the Yakima District (BCCHP), a federally funded aid program, administered through the Washington State Department of Health, which provides assistance and resources for women to undergo Pap tests, and for women who receive a diagnosis of an abnormal Pap test.

BCCHP and YVFWC will work with the study investigators to identify women who are non-compliant with Pap testing to monitor uptake of Pap test screening among randomized women via medical record review, and to develop and pilot test a patient navigator program to improve adherence and reduce time to follow-up after an abnormal Pap test.

To aid with issues regarding cultural relevance, a community advisory board was appointed and regular meetings are scheduled between the investigators and community members.

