### Sample size

Power is assessed for the primary endpoint, i.e. increased compliance with cervical cancer screening. We assume compliance probabilities will range from 0.15 to 0.30 for usual care, 0.30 to 0.45 for the low-intensity arm, and 0.45 to 0.60 for the high-intensity arm with at least a 0.15 difference between the low intensity and control arms and the low and high intensity arms. Assuming a 10% loss to follow-up these power calculations are based on a sample size of 180 in each of the three arms, assuming two Chi square tests will be conducted; one to compare the low intensity arm to the control arm and one to compare the high intensity arm to the control arm. The overall significance level for the two tests was targeted at 0.05 so that each test is powered with significance level 0.025 to account for the two primary evaluations.

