## Discussion

The ‘Cervical Cancer Screening and Adherence to Follow-up among Hispanic Women’ study has the potential to identify mechanisms to reduce health disparities in cervical cancer incidence through increasing uptake of cancer screening and thereby increasing early detection. The findings of this study will help address the disparate burden of cervical cancer among Hispanic women by implementing an innovative program to improve rates of cervical cancer screening, and it is the joint expectation of the research team and the clinic system that the clinic will continue to use the most effective and cost-effective intervention as part of its usual service to women in need of cervical cancer screening. Evaluation of a patient navigator program to aid Hispanic women in overcoming obstacles to receive follow-up care in a timely manner after a diagnosis of an abnormal Pap test, may help to increase the proportion of women who receive timely follow-up care in health care clinics in rural Eastern Washington. If successful, the patient navigator system may represent a method of reducing cancer morbidity and mortality, by removing cultural and other barriers and thus allowing women to successfully access appropriate healthcare after a diagnosis of a cervical abnormality.

Finally, the evaluation of cost-effectiveness of the intervention arms will aid in the design of appropriate inventions where financial constraints in underfunded health care systems may be of concern.

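### Cost per woman screened by arm is an average ratio: it credits each programme with women who would be screened anyway and hides the cost of moving from video to promotora

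*Protocol article*

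**What the plan says.** The third aim in the Background is "to assess the cost-effectiveness of each of the intervention programs", and the Abstract lists cost-effectiveness of the two programmes as an additional secondary endpoint. The only statement of the measure is in Primary outcome: "Cost-effectiveness analysis will examine the associated costs per woman screened, by intervention arm". No section mentions an increment over usual care or between the two programmes.

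Three other places bear on it:

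- **Sample size** gives the expected screening rates. For the comparator it reads: "We assume compliance probabilities will range from 0.15 to 0.30 for usual care". The video is put at 0.30–0.45 and promotora plus video at 0.45–0.60. The spacing it requires is "at least a 0.15 difference between the low intensity and control arms and the low and high intensity arms".
- **Control arm** says that usual-care women "will not receive any motivational messages or intervention materials from study staff".
- **Discussion** gives the intended use. The research team and clinic system expect that "the clinic will continue to use the most effective and cost-effective intervention as part of its usual service", and the closing paragraph of that section points to health systems short of funds.

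**The concern.** A programme's benefit is the screening it adds. The article expects a sizeable share of women to be screened with no study intervention, and those women sit in the denominator of both intervention ratios. Each programme therefore looks cheaper per unit of benefit than it is.

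The measure also does not fit the decision it is meant to inform. If usual care has no programme cost, its own ratio is 0. If every Pap test costs the same in all arms, usual care still has the lowest ratio. So the average cannot show whether either programme is worth buying. A clinic choosing between programmes needs the price of each extra woman screened by stepping up from the mailed video to the home visit, and an average by arm does not show it.

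**Working it through.** **Inputs.** Screening probabilities come from Sample size: usual care pC = 0.15–0.30, video pL = 0.30–0.45, promotora plus video pH = 0.45–0.60, with adjacent arms at least 0.15 apart. Programme cost per woman randomised is C, and usual-care programme cost is taken as 0 (assumption, consistent with the Control arm section). The article gives no unit cost, cost ratio or cost-effectiveness result, so there is no cost figure to reproduce. Its design figures are consistent: 180/0.90 = 200 per arm, and 3 × 200 = 600.

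**Step 1. Share of screened women who would be screened anyway, pC/p, at the minimum differences.**
- Video: 0.15/0.30 = 50% to 0.30/0.45 = 67%.
- Promotora plus video: 0.15/0.45 = 33% to 0.30/0.60 = 50%.

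**Step 2. Each programme versus usual care, programme cost only.** The average is C/p. Cost per additional woman screened is C/(p − pC). The understatement factor is p/(p − pC).

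| Programme | Usual care | Programme rate | Factor |
|---|---|---|---|
| Video, minimum difference | 0.15 | 0.30 | 0.30/0.15 = 2.0 |
| Video, minimum difference | 0.30 | 0.45 | 0.45/0.15 = 3.0 |
| Video, widest permitted difference | 0.15 | 0.45 | 0.45/0.30 = 1.5 |
| Promotora, minimum differences | 0.15 | 0.45 | 0.45/0.30 = 1.5 |
| Promotora, minimum differences | 0.30 | 0.60 | 0.60/0.30 = 2.0 |
| Promotora, widest permitted difference | 0.15 | 0.60 | 0.60/0.45 = 1.33 |

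Over all permitted rates the factor is 1.5–3.0 for video and 1.33–2.0 for promotora plus video.

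**Step 3. If each Pap test also costs s.** The factor becomes (C/d + s)/(C/p + s), with d = p − pC. Results at the minimum differences, with s as an assumption:
- s = C: video 1.77–2.38, promotora 1.34–1.62.
- s = 5C: video 1.40–1.62, promotora 1.15–1.25.

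**Step 4. Promotora versus video.** Let h be promotora cost divided by video cost (not given). Cost per extra woman over video, divided by the promotora average, is (1 − 1/h) × pH/(pH − pL).
- 0.30 vs 0.45: 3 × (1 − 1/h) = 2.0 at h = 3 and 2.7 at h = 10.
- 0.45 vs 0.60: 4 × (1 − 1/h) = 2.67 at h = 3 and 3.6 at h = 10.
- 0.30 vs 0.60, the widest permitted gap: 2 × (1 − 1/h) = 1.33 at h = 3 and 1.8 at h = 10.

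Example with video cost c, h = 3 and rates 0.45 and 0.60: the promotora average is 3c/0.60 = 5c per woman screened, but each extra woman over video costs 2c/0.15 = 13.3c.

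**Step 5. Does the order of the two programmes change?** The average favours video once h > pH/pL. Cost per additional woman versus usual care favours promotora while h < (pH − pC)/(pL − pC). The measures disagree between these limits.
- 0.15/0.30/0.45: from 0.45/0.30 = 1.5 to 0.30/0.15 = 2.
- 0.30/0.45/0.60: from 0.60/0.45 = 1.33 to 0.30/0.15 = 2.
- 0.15/0.30/0.60 (permitted, high arm above the minimum): from 0.60/0.30 = 2 to 0.45/0.15 = 3.

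The upper limit cannot exceed 3, because pH − pC is at most 0.45 and pL − pC at least 0.15. Adding the same s to every ratio leaves these limits unchanged.

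**The case against.** The strongest reply is that one condensed sentence is being read as a full definition. It says what the analysis will examine, and reporting by arm does not exclude an incremental ratio in a fuller document. The sentence before it commits to differences in screening between intervention and control arms, and Statistical analysis adds low versus high intensity. With costs by arm, a reader could form the incremental ratios. This stands in part: the article does not rule the increment out, and no data would be lost. But the only quantity it names is the average, and point estimates by arm give no uncertainty for an increment.

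Three stronger readings are tempting, and the documents do not support them.

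- **A reader might infer a two- to three-fold or greater understatement for both programmes.** Against usual care, two-fold is the ceiling for promotora plus video and three-fold for video. A factor above 3 arises only for promotora versus video. At 0.45 versus 0.60 it needs a promotora cost more than four times the video cost, since 4 × (1 − 1/4) = 3, and the article gives no cost ratio.
- **A reader might infer that the costlier arm is flattered more.** Against the common comparator, usual care, the video is understated more (2.0–3.0 versus 1.5–2.0 at the minimum differences). The opposite impression comes from changing the comparator to video for one arm only.
- **A reader might infer that the clinic would adopt the wrong programme.** At the minimum differences the order changes only for cost ratios from about 1.33–1.5 up to 2, and at no permitted rates above 3. Where the measures disagree, the average favours the cheaper video.

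It is also fair to say that removal of dominated arms and acceptability curves are analysis-plan detail. They are not needed here.

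**Conclusion.** The point holds as a criticism of the measure the article states. Cost per screened woman within an arm does not measure what a programme adds, and it cannot support the adoption choice described in the Discussion.

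The understatement versus usual care is 1.5- to 3.0-fold for video and 1.33- to 2.0-fold for promotora plus video. This rests on the article's planning rates, programme cost only, and a usual-care programme cost of 0. Including the Pap test lowers every factor. The promotora-versus-video figure of 2.0–3.6 rests on two conditions: an assumed cost ratio of 3 to 10, and a difference of exactly 0.15.

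The effect on the decision is narrower than these factors suggest. For most cost ratios both measures put the two programmes in the same order against usual care. What is then lost is the price of each extra woman screened by moving up. The primary analysis and the sample size are not affected.

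**What to change.** Replace the sentence in Primary outcome with one to this effect: cost-effectiveness will be measured as incremental cost per additional woman screened, for video versus usual care, promotora plus video versus usual care, and promotora plus video versus video, each with a confidence interval (for example by bootstrap). State which costs are counted, in particular whether the Pap test is included. Keep average cost per screened woman in each arm as a descriptive line.

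The cost is small: a sentence or two of text and a short additional analysis on costs and outcomes already planned, with no change to conduct or sample size. The figures will look less favourable to both programmes.

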### Secondary outcomes

As part of the reason for high cervical cancer mortality rates among Latinas is the lack of recommended follow-up, for abnormal Pap tests, a secondary outcome is compliance with such recommendations. The approach being used is a patient navigator approach where a *promotora* works closely with the participant to encourage her to attain the recommended follow-up.

The first patient navigator program was introduced by [name], in a successful effort to increase access to early effective medical care for breast cancer patients at the Harlem Hospital in New York City [21]. Patient navigators aid patients in navigating barriers to receiving care, such as competing demands of work, family responsibilities, transportation and childcare. In addition, Hispanic women may experience specific barriers to care such as culturally specific health beliefs, immigration status and language barriers that would make obtaining and completing optimal care more difficult [22].

Following formative work interviewing Hispanic women in the Yakima Valley who had received abnormal Pap test results, we developed a culturally-appropriate patient navigator program. Any participant, who receives a diagnosis of an abnormal Pap test after their initial cervical cancer screening, will be offered the services of a patient navigator. The patient navigator will contact the participant and guide them through potential barriers to care, such as transportation, childcare, financial impediments and cultural or linguistic barriers. Patient navigator contact will cease when the participant has successfully completed follow-up diagnostic care or treatment. Patient navigators will be selected from the different community partner organizations to work collaboratively and ensure sustainability of the program. Training will provide basic knowledge on cervical cancer screening as well as communicational skills. The secondary outcome will measure the time between diagnosis of the first abnormal Pap test, and attendance at the clinic for follow up. Elapsed time in participants assigned to a patient navigator will be compared to a similar population of women seen in the clinic who are not part of the study.

### Sample size

Power is assessed for the primary endpoint, i.e. increased compliance with cervical cancer screening. We assume compliance probabilities will range from 0.15 to 0.30 for usual care, 0.30 to 0.45 for the low-intensity arm, and 0.45 to 0.60 for the high-intensity arm with at least a 0.15 difference between the low intensity and control arms and the low and high intensity arms. Assuming a 10% loss to follow-up these power calculations are based on a sample size of 180 in each of the three arms, assuming two Chi square tests will be conducted; one to compare the low intensity arm to the control arm and one to compare the high intensity arm to the control arm. The overall significance level for the two tests was targeted at 0.05 so that each test is powered with significance level 0.025 to account for the two primary evaluations.

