### Statistical analysis

The primary end-point (Pap test compliance) will be coded as a binary variable. Evaluation of the success of the intervention is based only on Pap test compliance at follow-up. Chi square tests of 2 X 2 tables (compliance Yes/No by arm Control vs. High or Low intensity intervention) will be employed to assess whether intervention arms affects the probability of compliance at follow-up. We will randomize about 600 women (anticipated 200 per arm to each of 3 arms; control, low intensity intervention, high intensity intervention) into the study, which will allow for 10% attrition. Separate analysis will be conducted to compare the high intensity arm to the control arm and the low intensity arm to the control arm, and subsequent analysis will include comparing the low intensity arm to the high intensity arm as well as adjustment of the primary analysis by potential confounding characteristics such as race and age, to account for potential biases in the randomization.

Additional secondary analysis will include evaluating the effect of contact from a patient navigator to women who receive an abnormal Pap smear. All participants seen at the study clinics during the course of the study who receive an abnormal Pap smear (intervention population) will receive a contact from the patient navigator. These women will be compared to women who received an abnormal Pap smear at the same clinics between 180 and 90 days prior to the start of the study when no navigator calls were made (control population) as determined by medical records. The outcome measure will be determination of follow up for an abnormal Pap smear within 90 days of initial contact by the clinic. We will compare length of time from initial diagnosis to attendance at the clinic for recommended follow-up in the participants who have been contacted by the patient navigator, vs. the control population

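### The fixed 0.025/0.025 split is valid, but it gives up 5 to 8 points of power for video versus control that Holm's procedure would recover with the same data

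*Protocol article*

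**What the plan says.** The Sample size section of the protocol article names two primary chi-square tests: "one to compare the low intensity arm to the control arm and one to compare the high intensity arm to the control arm". It sets their level as follows: "The overall significance level for the two tests was targeted at 0.05 so that each test is powered with significance level 0.025". The power basis is 180 evaluable women per arm after 10% loss.

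The planned rates are stated as ranges: "compliance probabilities will range from 0.15 to 0.30 for usual care, 0.30 to 0.45 for the low-intensity arm", and 0.45 to 0.60 for high intensity. Adjacent arms are assumed to differ by at least 0.15. No power figure or power target is given.

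The Statistical analysis section repeats the two comparisons as "Chi square tests of 2 X 2 tables" and gives no further rule on levels. It adds that "subsequent analysis will include comparing the low intensity arm to the high intensity arm", grouped with covariate adjustment and without a level of its own. No stepwise or closed procedure is mentioned.

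**The concern.** The planned rates make the two primary tests very unequal in difficulty. A step of at least 0.15 between adjacent arms means at least 0.30 between high intensity and control, but possibly only 0.15 between video and control. A fixed split treats the two tests alike. The easy test hardly needs its 0.025, and the rule does not release that 0.025 once the test has succeeded. The harder test is held to 0.025 in every case.

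What is at stake is the chance of detecting a real benefit of the mailed video, the simpler of the two programs. In the upper part of the planned range that chance falls below 80%, a conventional benchmark that the article itself does not set.

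**Working it through.** **Inputs.** From Sample size: 180 evaluable per arm, 0.025 per test, and the planned rates. From Statistical analysis: about 200 randomized per arm and 2 × 2 chi-square tests, taken as two-sided and uncorrected for continuity.

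**The plan's own figures.** 200 × (1 − 0.10) = 180, and 0.025 + 0.025 = 0.05. Both reproduce.

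**Power under the fixed split.** With p̄ the mean of the two rates and d their difference,

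power = Φ{ [d√n − z√(2p̄(1−p̄))] / √(p₁(1−p₁) + p₂(1−p₂)) },

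where z = 2.241 at level 0.025 and 1.960 at level 0.05.

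- Video vs control, 0.30 vs 0.45: d√n = 0.15 × 13.416 = 2.012; √(2 × 0.375 × 0.625) = 0.685; √(0.21 + 0.2475) = 0.676. At 0.025: (2.012 − 2.241 × 0.685)/0.676 ≈ 0.71, power 76.0%. At 0.05: (2.012 − 1.960 × 0.685)/0.676 ≈ 0.99, power 83.9%.
- Video vs control, 0.15 vs 0.30: 88.2% at 0.025 and 93.0% at 0.05.
- High intensity vs control, 0.30 vs 0.60: 99.99% at 0.025. At 0.15 vs 0.45 it is 100% to four decimals.

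**Power under Holm.** Holm tests the smaller of the two p-values at 0.025 and, only if that is rejected, the other at 0.05. Since high versus control is rejected almost always, video versus control is in effect tested at 0.05. Simulation with 180 per arm and 1,000,000 trials per scenario gives, for video versus control:

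| Control / video / high | Fixed 0.025, formula | Fixed 0.025, simulated | Holm, simulated | Gain over simulated fixed (points) |
|---|---|---|---|---|
| 0.15 / 0.30 / 0.45 | 88.2% | 88.8% | 93.3% | 4.6 |
| 0.20 / 0.35 / 0.50 | 83.1% | 83.6% | 89.7% | 6.1 |
| 0.25 / 0.40 / 0.55 | 79.0% | 79.3% | 86.4% | 7.1 |
| 0.30 / 0.45 / 0.60 | 76.0% | 76.4% | 84.0% | 7.6 |

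(Gains are taken before rounding.) High versus control stays at 99.98% or more in every row under both rules.

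**Error control.** When both nulls are true, Holm makes at least one rejection exactly when Bonferroni does, so the familywise error is the same: 4.6% with all rates 0.15 and 4.7% with all rates 0.30. When only the video null is true, the simulated false-rejection rate is 4.5% (0.15/0.15/0.30) and 5.04% (0.30/0.30/0.60). The small excess in the last figure reflects the large-sample chi-square test: a single unadjusted test with both rates 0.30 has a simulated size of 5.09%.

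**Away from the planned gradient.** If both programs work equally (0.30/0.45/0.45), Holm raises video versus control from 76.3% to 81.4%. If only the video works (0.30/0.45/0.30), it moves from 76.5% to 76.6% (400,000 trials), which is almost nothing, because high versus control is then rarely rejected and passes nothing on.

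**The case against.** The strongest reply is that nothing here is wrong. The split is correct for the two tests named and familywise error is below 0.05. Bonferroni also yields simple simultaneous confidence intervals. That stands: this is a matter of efficiency, not an error in alpha. Nor is a target missed. The article states no target, the 0.15 difference is a minimum, and power is below 80% only from about 0.25 vs 0.40 upward.

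It may also be said that 0.025 appears as a level for powering, and that a fuller analysis plan could already use a stepwise rule. That is possible, but the rule as published is a fixed split, and it is the only one at hand.

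A reader might go further and infer that low versus high intensity has been left outside error control although it decides which program is kept. The Discussion does expect that "the clinic will continue to use the most effective and cost-effective intervention as part of its usual service". But that is an expectation in which cost also counts, and the article makes low versus high a subsequent analysis, which may properly sit outside a budget set for two primary tests. Adding that comparison at an unadjusted 0.05 would give an 8.5–8.7% chance of some false rejection under the global null. That figure assumes a level the article does not state and a three-test family it does not define, so it does not show the stated 0.05 to be exceeded.

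The same reader might prefer a closed three-arm test: a global chi-square at 0.05, then each pairwise test at 0.05. It does bring low versus high into the family, at 82–84% power under the planned rates. It is not uniformly better than the present rule. At 0.30/0.40/0.45, high versus control has 75.5% power against 76.4% now, and the chance of any success against control is 77.1% against 80.2%.

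**Conclusion.** The point holds as one of efficiency. Under the planned rates, the fixed split costs video versus control about 5 to 8 percentage points of power: 76–89% instead of 84–93% at 180 per arm. Nothing is gained in return for high versus control, which succeeds almost always under either rule.

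The size rests on three assumptions: 180 evaluable women per arm, two-sided uncorrected chi-square tests, and a high-intensity effect near the planned 0.30. The gain shrinks towards nil as that effect disappears. One part needs none of these assumptions: Holm never rejects less than the current rule.

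The documents do not support reading this as an invalid analysis, a missed power target, or a loss of error control through low versus high.

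**What to change.** In both Sample size and Statistical analysis, state that the two comparisons with control will be tested by Holm's procedure at an overall 0.05: the smaller p-value at 0.025 and, if that is rejected, the other at 0.05. The 0.025 can stay as the conservative level for powering. The change should be made before outcome data are seen.

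Low versus high can remain a subsequent analysis. A closed three-arm test is an option only if the sponsor wants that comparison inside the primary family and accepts the trade-off described above.

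The cost is a sentence or two of text, with no added participants or data. The one drawback is that simultaneous confidence intervals matching the test decisions are less direct than under Bonferroni.
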